#### Efficacy analysis

The annual rate of change in eGFR from 12 to 104 weeks (chronic eGFR slope) will be analyzed using a random coefficient model. In this model, fixed effects comprise the treatment group, observation time point, and the interaction between the treatment group and observation time point; random effects comprise the intercept and observation time point. Chronic eGFR slope will be compared between the treatment and control groups in the following order: (i) the non-inferiority of the pemafibrate group to the control group will be examined. Non-inferiority will be concluded if the lower limit of the 95% confidence interval (CI) for the eGFR slope in the pemafibrate group compared with the control group is >−0.5. (ii) The superiority of the pemafibrate group will be examined if non-inferiority is achieved. The difference will be considered statistically significant when the lower limit of the 95% CI for the eGFR slope in the pemafibrate group compared with the control group is >0.0. Randomization will be stratified by age, baseline eGFR category, diabetes status, and hypertension status. These stratification factors will be adjusted as covariates in the primary analysis model because they are established predictors of eGFR decline and are expected to reduce residual variance.

The annual rate of change in eGFR during the 104-week study period (total eGFR slope) will be analyzed using the same procedure as that for chronic eGFR slope. Regarding changes in other variables, the least-squares mean, and its 95% CI for each visit will be calculated using the mixed-effects models for repeated measures, and differences between the groups will be calculated. Comparisons between the groups will be performed using the unpaired *t*-test. The proportions of participants in each CKD stage and grade of urinary protein qualitative evaluation will be evaluated using the Chi-square test. Regarding the outcome measures, the incidence rates will be calculated using the person-year method, and survival curves will be confirmed using the Kaplan–Meier method. When adjusting for covariates, a Cox proportional hazards model will be used to calculate hazard ratios. Stratified analyses will be performed for the endpoints, such as by fasting or non-fasting status, medical history, or concomitant medications. Sensitivity analysis will also be performed to adjust for potential confounding factors, such as sex or UACR at enrollment.

Given that the primary endpoint is based on eGFR, additional sensitivity analyses will be performed. These analyses will exclude participants with conditions that potentially bias eGFR estimation, such as severe obesity (e.g. body mass index ≥35 kg/m²), nephrotic-range proteinuria (e.g. UPCR ≥3.5 to ≤5.0 g/g Cr), or marked malnutrition (e.g. body mass index <18 kg/m² or albumin <3.0 g/dl), to assess the robustness of the primary findings.

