#### Follow up

The study schedule is summarized in Supplementary Table 1. Follow-up visits are scheduled at 12 and 26 weeks and then every 26 weeks until 104 weeks. After 104 weeks of observation, participants in the pemafibrate group will stop taking pemafibrate and continue conventional therapy, and will be assessed 8 weeks after discontinuation. Participants in the control group will continue conventional treatment and will be assessed 8 weeks after the 104-week visit. Adherence to study treatment will be assessed by asking participants about missed doses. Blood pressure, pulse rate, and body weight measurements will be obtained at each visit. Blood and urine laboratory tests will also be performed at each visit. Laboratory parameters will be assessed using routine methods in participating medical facilities. In principle, fasting blood samples will be collected (≥10 hours after the last meal). If non-fasting blood samples are collected at baseline, non-fasting blood samples will also be collected during follow up. Details of the laboratory measurements are shown in Supplementary Table 2. LDL-C (direct method) and cystatin C will also be measured if possible (i.e. with insurance coverage). LDL-C (calculated), non-HDL-C, TG/HDL-C ratio, small dense LDL-C, TG-rich lipoprotein cholesterol, eGFR, and eGFR based on cystatin C (eGFR-cys) will be calculated using the formulas described in the Supplementary Methods (Supplementary File 2). Urinalysis will be performed on spot urine samples to assess UACR, if possible (i.e. with insurance coverage), or UPCR. At each visit, concomitant medications, cardio-kidney events, and adverse events (AEs) will be verified by the investigators.

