#### Endpoints

The primary endpoint of the JKAPI-CKD study is the chronic eGFR slope from 12 to 104 weeks, thereby excluding potential acute changes in eGFR. Chronic eGFR slope is a proposed surrogate marker for kidney events [20, 21]. The key secondary endpoint is total eGFR slope calculated from randomization until week 104. Other secondary and safety endpoints are shown in Table 2. In the present study, some pre-specified subgroup analyses are planned (Supplementary Table 3), including analyses of the stratification factors used in the randomization process (baseline eGFR category, presence of diabetes, and presence of hypertension). Outcomes in the subgroups will be examined to test for interaction effects.

**Table 2: tbl2:** Outcomes.

Primary endpoint
Chronic eGFR slope from 12 to 104 weeks, after study start

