**Secondary endpoints**
Key secondary endpoint
Total eGFR slope during the 104-week study period
Efficacy endpoints
Change from baseline in the following items at each visit
Lipid metabolism^a^
TG, HDL-C, TC, LDL-C, non-HDL-C, TG/HDL-C, and TRL-C
Kidney function
eGFR, Cr, UPCR, UACR, and predicted ACR^b^
Change in proportion of CKD stages between baseline and 104-week visit
Proportion of CKD stage transition between baseline and 104-week visit
Liver function
AST, ALT, γ-GTP, and ALP
Others
CK, BUN, uric acid, total protein, albumin, CRP, RBC, WBC, blood glucose^a^, Hb, Hct, platelet count, HbA1c (diabetic patients only), BNP (NT-proBNP) (heart failure patients only)
Outcomes
Incidence of composite kidney events, and components of kidney events
Incidence of composite CVEs, and components of CVEs
Incidence of rhabdomyolysis
Incidence of acute kidney injury
Physical findings
Body weight, body mass index, blood pressure (rest sitting position), pulse rate
Exploratory items
eGFR-cys, and cystatin C
Comparison of eGFR slope before the study and during the study^c^
Change from baseline in the above items at each visit and 8 weeks after 104-week visit in the cases with data available
Correlation between change in TG and other variables
Safety evaluation
Incidence of severe AEs
Incidence of AEs
Incidence of severe side-effects related to the study drug
Incidence of side-effects related to the study drug

a Lipid metabolism-related items and blood glucose analyzed separately for fasting and non-fasting blood samples.

b predicted ACR = exp 5.2659 + 0.2934 × log [min (PCR/50, 1)] + 1.5643 × log {max [min (PCR/500, 1), 0.1]} + 1.1109 × log [max (PCR/500, 1)] − 0.0773 × (if female) + 0.0797 × (if diabetic) + 0.1265 × (if hypertensive).

c eGFR slope during the study includes both chronic and total eGFR slopes. ACR, albumin-to-creatinine ratio; ALP, alkaline phosphatase; ALT, alanine aminotransferase; AST, aspartate aminotransferase; BNP, brain natriuretic peptide; BUN, blood urea nitrogen; CK, creatine kinase; Cr, creatinine; CRP, C-reactive protein; CVE, cardiovascular event; eGFR-cys, eGFR based on cystatin C; γ-GTP, gamma-glutamyl transpeptidase; Hb, hemoglobin; HbA1c, hemoglobin A1c; Hct, hematocrit; HDL-C, high-density lipoprotein cholesterol; LDL-C, low-density lipoprotein cholesterol; NT-proBNP, N-terminal pro BNP; RBC, red blood cell count; TC, total cholesterol; TRL-C, TG-rich lipoprotein cholesterol; WBC, white blood cell count.

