### Statistical analysis

#### Sample size

On the basis of a previous study [20] and a guideline [21], a difference of 0.5–1.0 ml/min/1.73 m^2^/year in eGFR slope has been shown to be associated with a >97.5% probability that the drug will also reduce the risk of kidney failure. Therefore, we defined a difference of 0.5 ml/min/1.73 m^2^/year in eGFR slope between the study groups as a non-inferiority margin, assuming that the standard deviation (SD) would be 4.0 [22]. This SD estimate was based on a previous study of Japanese patients with type 2 diabetes and renal dysfunction [22]. This estimate was considered appropriate because it was derived from clinic-based real-world data in Japan, which closely reflects the multicenter clinical setting and patient characteristics of the present study. Moreover, because the JKAPI-CKD study applies rigorous inclusion and exclusion criteria (e.g. eGFR ≥20 and <60 ml/min/1.73 m² and exclusion of severe proteinuria), the study population is expected to be more homogeneous than general real-world cohorts, further supporting the validity of this assumption. The target enrollment of 2200 participants was calculated to detect a difference in the primary endpoint of 0.5 ml/min/1.73 m^2^/year eGFR slope difference with a power of 80% and an alpha error of 2.5%, accounting for a potential 10% drop-out rate.

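### The primary slope model leaves baseline albuminuria to a sensitivity analysis, so some precision on the primary comparison may be lost

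*Protocol article*

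**What the plan says.** The Endpoints section states: "The primary endpoint of the JKAPI-CKD study is the chronic eGFR slope from 12 to 104 weeks". Under Efficacy analysis, the random coefficient model has fixed effects for group, time and their interaction, and a random intercept and time effect. On covariates it says: "These stratification factors will be adjusted as covariates in the primary analysis model because they are established predictors of eGFR decline". Registration and randomization lists these factors, each with two levels: age (cut at 65), eGFR (cut at 45), diabetes and hypertension. Total slope, the key secondary endpoint, is analyzed in the same way.

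Albuminuria enters later in the same section: "Sensitivity analysis will also be performed to adjust for potential confounding factors, such as sex or UACR at enrollment". The Follow up section describes its measurement: "Urinalysis will be performed on spot urine samples to assess UACR, if possible (i.e. with insurance coverage), or UPCR". Table 2 lists UPCR, UACR and a predicted ACR among the variables analyzed as change from baseline, and its footnote gives a formula for predicting ACR from PCR. A pre-study slope appears once, among the exploratory items in Table 2: "Comparison of eGFR slope before the study and during the study".

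**The concern.** The plan adjusts because the chosen variables predict eGFR loss and should lower unexplained variation. That reason applies equally to baseline albuminuria. The Sample size section itself counts the exclusion of severe proteinuria as making the population more homogeneous. The exclusion removes only UPCR above 5 g/g or UACR above 3000 mg/g, so a wide range remains, and albuminuria is not a randomization factor.

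Placing UACR among possible confounders understates its use. In a randomized comparison, the main value of a prognostic baseline variable is a narrower confidence interval. Both primary decisions (lower 95% limit above -0.5, then above 0.0) depend on the width of that interval. Enrollment is complete, so more participants are no longer a source of precision.

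The point concerns which baseline values are in the model. It does not concern how the stratification factors enter it.

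**Working it through.** **Inputs from the Sample size section.** The difference is 0.5 ml/min/1.73 m² per year, used "in eGFR slope between the study groups as a non-inferiority margin" and also as the difference to detect. The SD of slope is 4.0. The calculation is made "with a power of 80% and an alpha error of 2.5%, accounting for a potential 10% drop-out rate". The 2.5% is read as one-sided, which matches the 95% interval rule. Allocation is 1:1, the target is 2200, and 2328 were enrolled (Results).

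**The plan's own figure.**
- n per arm = 2 × (1.960 + 0.842)² × 4.0² / 0.5² = 1005, or 2010 in total.
- Allowing for 10% drop-out: 2010 / 0.9 = 2234, or 2010 × 1.1 = 2211. Both are close to 2200, so the target reproduces.
- Reading 2.5% as two-sided gives 1217 per arm and 2705 after drop-out, which does not reproduce.

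**Power without further covariates.**
- 2200 less 10% is 990 per arm. SE = 4.0 × √(2/990) = 0.180. Power = Φ(0.5/0.180 − 1.96) = 79.4%. The 95% half-width is 0.352.
- 2328 less 10% is about 1048 per arm. Power is 81.6%.

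**Power with further covariates.** Let R² be the share of slope variance that the added covariates explain beyond the strata, taking 4.0 as the SD before they are added. Then SE becomes SE × √(1 − R²). The documents give no value for R², so the range is an assumption.

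| R² (assumed) | Half-width, 990 per arm | Power, 990 per arm | Power, 2328 enrolled |
|---|---|---|---|
| 0 | 0.352 | 79.4% | 81.6% |
| 0.02 | 0.349 | 80.2% | 82.4% |
| 0.05 | 0.343 | 81.4% | 83.5% |
| 0.10 | 0.334 | 83.4% | 85.4% |

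**The form of the term matters.** A main effect shifts the level of a participant's eGFR line by the same amount at every visit. It leaves the spread of slopes between participants unchanged. This was checked in a small simulation: five replicates, 990 per arm, visits at weeks 12, 26, 52, 78 and 104, an assumed residual SD of 2.5, individual slope estimates with SD 4.0, and R² of 0.10. The mean SE of the group-by-time term was:
- 0.1794 with no covariate;
- 0.1794 with the covariate as a main effect;
- 0.1694 with the covariate and its interaction with time (the formula gives 0.180 × √0.9 = 0.171).

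Only the interaction with time narrows the slope contrast.

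**Availability of the two candidate covariates.**
- Albuminuria: urine is tested at each visit and yields UACR or UPCR. Exclusion criterion 3 uses one or the other before consent. The Table 2 footnote supplies the conversion.
- Pre-study slope: the article gives no source, look-back window, number of values or completeness. Eligibility rests on the latest eGFR within 16 weeks before consent, and a single value gives no slope.

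**The case against.** The strongest reply is that nothing here is wrong. Adjusting for all the randomization factors is a valid, prespecified choice. The sample size takes no stated credit for adjustment, and its power is met on its own inputs without further covariates. UACR adjustment is already planned as a sensitivity analysis, and another analysis excludes nephrotic-range proteinuria. A condensed article need not defend each covariate that it omits. All of this stands, and it limits the point to an improvement.

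Two further objections also stand. First, any gain must come on top of age, eGFR, diabetes and hypertension. The predicted ACR uses diabetes and hypertension in its formula, so it partly overlaps with the strata. Second, the trial is open-label and fully enrolled, so a change to the primary model while eGFR data accumulate could look data-driven. Fixing it merely before database lock would be too late.

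A reader might go further and infer that the trial already holds each participant's earlier eGFR slope, the baseline counterpart of the primary outcome, and discards it. The documents do not support this. They name one exploratory comparison and do not show that the values exist for most participants. A slope from a few routine creatinine values would also be a noisy predictor.

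The objections do not remove the case for albuminuria. It is measured, it can be put on one scale, and it meets the plan's own reason for adjusting.

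**Conclusion.** The point holds as a missed gain in efficiency, of unknown and probably modest size. The randomized comparison is unbiased as planned and the target of 2200 is sound. At 990 per arm the gain is about 0.8, 2.0 or 4.0 percentage points of power if the added covariates explain 2%, 5% or 10% of slope variance beyond the strata. With 2328 enrolled it is about 3.8 points at 10%.

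These figures rest on three assumptions: an SD of 4.0, 10% drop-out, and an R² that the documents do not give. Larger gains can be calculated. A correlation of 0.5, for example, means R² of 0.25 and power of 89.5% at 990 per arm, but nothing in the documents supports a value that high. Nor does the omission make the trial underpowered on its own terms.

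**What to change.** Amend the Efficacy analysis text, and the analysis plan to match, before any look at eGFR data by arm:

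1. Add log baseline ACR and its interaction with time to the primary random coefficient model, for both chronic and total slope. Use measured UACR, otherwise the ACR predicted from UPCR.
2. Where the baseline value is missing, use the overall mean with a missing-value indicator, so that no participant drops out of the model.
3. Keep the four stratification factors, and report the model as now written as the sensitivity analysis.
4. Check, blinded and pooled over arms, how many participants have enough pre-randomization eGFR values to calculate a slope. If most do, add the pre-study slope and its interaction with time. Otherwise leave it exploratory.

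The cost is wording, a few lines of code and a documented, dated amendment. The albuminuria term needs no new measurement. The drawbacks are that baseline ACR would mix measured and predicted values, and that the published primary model would become the sensitivity analysis.

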Pemafibrate is a novel selective peroxisome proliferator-activated receptor alpha modulator that improves lipid profiles and is excreted primarily in the bile [13]. Unlike conventional fibrates, pemafibrate can be used safely in patients with severe CKD. In a phase IV study, no significant changes in the pharmacokinetics of pemafibrate were observed in patients with severe CKD (eGFR <30 ml/min/1.73 m^2^) or in those receiving maintenance dialysis compared with patients with mild-to-moderate CKD (i.e. eGFR ≥30 and <60 ml/min/1.73 m^2^) [14]. *Post hoc* analyses by subgroups stratified on the basis of baseline eGFR showed that pemafibrate exerted TG-lowering effects and did not worsen kidney function regardless of baseline CKD stage during 52 weeks of follow up in a multicenter, single-arm, open-label, phase III trial [15]. However, in the PROMINENT trial, which was a large RCT assessing the efficacy of pemafibrate on CV outcomes in patients with type 2 diabetes, increased serum creatinine levels and decreased eGFR were observed during pemafibrate administration [24]. Notably, these changes were reversible after discontinuation of pemafibrate. The changes in serum creatinine and eGFR observed with pemafibrate may, at least in part, reflect its effects on glomerular hemodynamics [25–27] because patients with diabetes often develop glomerular hyperfiltration. Some small observational studies reported that switching from conventional hypertriglyceridemia treatment, including fibrates, to pemafibrate did not lead to an increase in serum creatinine or a decline in eGFR, in patients with CKD, not limited to those with diabetic nephropathy [16, 17]. Notably, switching from conventional fibrates to pemafibrate was associated with improved kidney function, as evidenced by reduced serum creatinine levels and increased eGFR [16, 17]. An RCT is ongoing to examine the effect of pemafibrate on proteinuria in patients with CKD [28]. However, this study is relatively short in duration and small in sample size, and therefore does not provide meaningful information about the effect of pemafibrate on GFR. The JKAPI-CKD study will evaluate the effect of pemafibrate on kidney function using eGFR-cys or a subgroup analysis by the presence or absence of diabetes.

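### Total eGFR slope is fitted as one straight line from randomization, which would understate any lasting acute loss before week 12 and loosen a −0.5 non-inferiority test

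*Protocol article*

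**What the plan says.** Under Efficacy analysis, the chronic slope (weeks 12 to 104) is analysed with a random coefficient model. Its fixed effects are treatment, time and their interaction, its random effects are intercept and time, and the stratification factors are covariates. Non-inferiority is tested first (lower 95% limit above −0.5), then superiority (lower limit above 0). The next paragraph says that total slope "will be analyzed using the same procedure as that for chronic eGFR slope". No knot, second slope or change-over-time estimator is described.

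Under Endpoints: "The key secondary endpoint is total eGFR slope calculated from randomization until week 104". The same paragraph explains why the primary starts at week 12, "thereby excluding potential acute changes in eGFR". The Discussion reports that in one earlier large trial in type 2 diabetes "increased serum creatinine levels and decreased eGFR were observed during pemafibrate administration", and adds that this was reversible after stopping.

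**The concern.** A single line is a reasonable shape after week 12, because the acute phase has been cut off. From randomization, the same line must describe a possible early step and a later chronic slope together. Because the model has a treatment main effect, the fitted intercepts of the two groups can differ, and they absorb much of a step that occurs by week 12. The fitted slope difference is then no longer the mean annual change over 104 weeks, and it depends on visit spacing and on the timing of dropout.

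The primary leaves the acute period out by design, so total slope is the slope endpoint that could show whether an early loss offsets a chronic benefit. If it counts only part of that loss and is then held against a −0.5 margin, non-inferiority could be declared too easily.

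**Working it through.** **Inputs from the article.** Visits at weeks 12, 26, 52, 78 and 104 (Follow up), plus baseline at week 0. Margin: "we defined a difference of 0.5 ml/min/1.73 m^2^/year in eGFR slope between the study groups as a non-inferiority margin". Slope SD: "assuming that the standard deviation (SD) would be 4.0". Error rates: "with a power of 80% and an alpha error of 2.5" per cent. Dropout: "accounting for a potential 10% drop-out rate". Target 2200 and enrolled 2328, randomized 1:1.

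**Assumption.** The size and timing of an acute effect are not given. I take a loss A, complete by week 12 and constant afterwards, on top of a chronic difference c per year, with A from 0.5 to 2.0.

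**Step 1: the plan's own sample size.** n per arm = 2 × 4.0² × (1.960 + 0.842)² / 0.5² = 1005. Dividing by 0.9 gives 1117 per arm (2234 in total); multiplying by 1.1 gives 1106 (2212). Both are within 3% of 2200, so alpha is one-sided 2.5%.

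**Step 2: what the line returns.** With complete balanced data, the random intercept and slope model gives the least-squares slope (checked by direct generalized least squares). For weeks 0, 12, 26, 52, 78, 104 the mean is 45.33 and Sxx = 8093.3. The slope of a unit step after week 0 is 45.33 / 8093.3 = 0.00560 per week, or 0.291 per year.

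- Fitted difference: c − 0.291A per year.
- True mean annual change over 104 weeks: c − A/2 = c − 0.500A per year.
- Ratio for the acute part: 0.291 / 0.500 = 0.583, an understatement of 42%.
- Group difference in fitted intercept at time 0: −0.579A, although randomization makes the expected baseline difference zero.

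**Step 3: incomplete data.** Dropout was spread evenly over the visits, with assumed intercept SD 11, slope SD 2 or 4 and residual SD 2, 4 or 6. The ratio is 0.599–0.647 at 10% dropout (understatement 35–40%) and 0.618–0.720 at 20% (28–38%). If baseline is sampled 8 weeks before treatment starts, the ratio is 0.656 (34%).

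**Step 4: non-inferiority error.** Set c so that the true difference is exactly −0.5. The fit is then −0.5 + 0.209A, and the false non-inferiority rate is Φ(0.209A/SE − 1.96). With 2200 × 0.9 / 2 = 990 per arm, SE = 4.0 × √(2/990) = 0.180.

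| A | c | Fitted difference | False non-inferiority |
|---|---|---|---|
| 0.5 | −0.25 | −0.396 | 8% |
| 1.0 | 0 | −0.291 | 21% |
| 1.5 | 0.25 | −0.187 | 41% |
| 2.0 | 0.50 | −0.083 | 64% |

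This SE borrows the SD of 4.0 for total slope. Alternatively, keep 4.0 for the chronic slope and derive the total-slope SD: 16 = τ² + σ²/2.081, and total SD = √(τ² + σ²/2.993), where τ is the between-person slope SD, σ the residual SD and time is in years. For τ = 2, 3 and 3.5 the total SD is 3.51, 3.72 and 3.85. With 2328 × 0.9 / 2 ≈ 1047 per arm, the SE is 0.154, 0.163 and 0.168, and the error at A = 1.0 is 27%, 25% and 24%. At A = 0.5 it is 9–10%.

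With equal chronic slopes (c = 0), the fitted line reaches −0.5 only at A = 0.5/0.291 = 1.72, where the true difference is −0.86 per year.

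**The case against.** Four points on the other side have weight.

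- **An acute fall is only a possibility.** A reader might infer that the plan expects one. Endpoints calls acute changes potential, and the Discussion is mixed. It reports no worsening over 52 weeks in a phase III post hoc analysis and no creatinine rise in small CKD studies after switching to pemafibrate. The fall in the earlier large trial comes without size or timing. This stands, and the conclusion is conditional on it.
- **The fall would not be hidden, and total slope is not called confirmatory.** Table 2 lists change in eGFR and creatinine at each visit, analysed by repeated-measures models, so a week-12 difference will be reported. A reader might also take total slope as a confirmatory endpoint under alpha control; the article never says so. That the −0.5 margin applies to it is inferred from the shared procedure. This stands too, but no margin is attached to the by-visit changes.
- **The reference value is a choice of estimand.** A least-squares trend is also an annual rate of change, and the article does not define total slope as change divided by time. That is fair, but a trend whose value moves with visit spacing and dropout (step 3) is a poor target for a fixed margin.
- **A condensed article may leave time modelling to the full plan.** The full plan might add a knot. But the article lists the model terms and sends total slope through them, so the stated method is the one reviewed here.

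**Conclusion.** The concern holds in conditional form. As stated, the model for the key secondary endpoint does not fit the time course that the article itself allows for. If pemafibrate causes a loss by week 12 that persists, total slope understates that component by about 42% with complete data and by roughly 28–40% with 10–20% dropout. If the −0.5 margin is applied, the test is then anticonservative: about 8% error at an assumed A of 0.5 and about 21–27% at 1.0, against 2.5%. These rates rest on assumed values of A and on the step shape; the documents supply neither.

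The documents do not support the unconditional reading that the non-inferiority test is anticonservative. Without an acute effect there is no such bias, and with an acute gain the test is conservative. The primary endpoint is unaffected. The change is worth making before analysis but does not threaten the main result.

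**What to change.** For the key secondary, prespecify a two-slope (linear spline) mixed model with a knot at week 12, fitted to all eGFR values from baseline:

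- group × acute-time and group × chronic-time terms;
- either a common baseline mean, justified by randomization, or a group intercept;
- random effects for intercept, chronic slope and, where estimable, acute change;
- total slope = (12 × acute + 92 × chronic) / 104, which returns c − 0.500A under the step assumption.

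State whether the −0.5 margin applies to total slope. Keep the single-line fit as a sensitivity analysis.

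The cost is a clarified paragraph and a little code. No new data are needed, and with the study period scheduled to June 2029 the change can still be prespecified. The price is precision. If acute change does not vary between people, the slope SD rises from 3.51–3.85 to 3.77–3.93, so the standard error is about 2–7% larger. If acute change varies with an assumed SD of 2–4 ml/min/1.73 m², it is about 4–15% larger. Only baseline and the week-12 visit bracket the acute segment, so its random effect may not be estimable; a fallback structure should be named in advance.

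### For the change-from-baseline secondary endpoints other than the eGFR slopes, the plan estimates by MMRM but tests by an unpaired t-test, so estimate and p-value come from different procedures

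*Protocol article*

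**What the plan says.** Table 2 of the protocol article defines a long list of secondary variables (lipids, kidney function, liver enzymes, other laboratory values) as "Change from baseline in the following items at each visit". The Follow up section gives the visits: "Follow-up visits are scheduled at 12 and 26 weeks and then every 26 weeks until 104 weeks", that is, weeks 12, 26, 52, 78 and 104.

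The Efficacy analysis section then makes two consecutive statements about these variables:

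- Estimation: the "least-squares mean, and its 95% CI for each visit will be calculated using the mixed-effects models for repeated measures, and differences between the groups" are to be calculated.
- Testing: "Comparisons between the groups will be performed using the unpaired" *t*-test.

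Two other statements in the same section limit the scope. The key secondary endpoint, total eGFR slope, "will be analyzed using the same procedure as that for chronic eGFR slope", so it is judged in the random coefficient model. On covariates, the article says "These stratification factors will be adjusted as covariates in the primary analysis model". It lists no covariates for the MMRM.

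**The concern.** One comparison is given two analyses. The MMRM uses all visits jointly and can carry covariates. The two-sample t-test on change at a visit uses that visit and baseline only, carries no covariates, and drops anyone without a value at that visit. The article does not say which result governs if they differ.

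At stake is how the lipid, albuminuria and eGFR-by-visit results will be reported. Triglyceride is the variable to which pemafibrate is titrated, so its change is among the results readers will look at first. Table 2 also has lipids and glucose analysed separately for fasting and non-fasting samples, so each of those comparisons rests on fewer participants and precision matters more. A model-based difference set beside a p-value from another method invites a report in which the two point in different directions.

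**Working it through.** **1. The plan's own figure.** The article gives no power or sample size for these secondary comparisons. Its one figure is 2200 for the primary endpoint, "with a power of 80% and an alpha error of 2.5"%, with SD 4.0, a difference of 0.5 and 10% drop-out.

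- n per arm = 2 × (1.960 + 0.842)² × 4.0² / 0.5² ≈ 1005, or 2010 in total.
- Allowing for drop-out: 2010 / 0.9 ≈ 2234, or 2010 × 1.1 = 2211.

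Both are close to 2200, with 2.5% read as one-sided. Nothing below changes this number.

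**2. Precision of the two tests.** Assume equal variance σ² at baseline and follow-up, with correlation r. The documents do not give r, so a range is shown.

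- Variance of a change score: 2σ²(1 − r).
- Residual variance after adjusting for baseline: σ²(1 − r²).
- Ratio, adjusted to change score: (1 − r²) / [2(1 − r)] = (1 + r)/2.

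The t-test's variance is therefore larger by a factor of 2/(1 + r), and its standard error by √[2/(1 + r)]. Where the adjusted model has 80% power at two-sided 5%, the t-test's power is Φ[(1.960 + 0.842) × √((1 + r)/2) − 1.960].

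| r (assumed) | Adjusted variance as share of t-test variance | Increase in SE with t-test | t-test power when adjusted model has 80% |
|---|---|---|---|
| 0.5 | 75% | 15.5% | 67.9% |
| 0.7 | 85% | 8.5% | 73.3% |
| 0.9 | 95% | 2.6% | 78.0% |

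The comparator is a baseline-adjusted model, which is what the fix proposes. The article does not say that its MMRM adjusts for baseline.

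**3. How often the two would disagree.** A simulation compared a baseline-adjusted repeated-measures model with an unpaired t-test on change at week 104. Settings: 2200 participants, the five scheduled visits, about 9% drop-out by week 104, compound-symmetric covariance treated as known, and 1500 runs per scenario. Disagreement means that one result is significant at two-sided 5% and the other is not.

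| r (assumed) | Power, model | Power, t-test | Disagreement, true effect | Disagreement, no effect, random drop-out |
|---|---|---|---|---|
| 0.5 | 81.1% | 67.8% | 17.9% | 5.7% |
| 0.7 | 79.9% | 74.6% | 11.2% | 3.9% |
| 0.9 | 80.9% | 77.3% | 6.3% | 2.5% |

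**4. Validity.** With no true effect, rejection rates ran from 4.5% to 6.2% over both methods. This includes scenarios where drop-out depended on the last observed value, in opposite directions in the two arms. The simulation standard error at 5% is √(0.05 × 0.95 / 1500) ≈ 0.6 percentage points, so these rates are near nominal. The average estimated effect was within 0.002 SD of zero for both methods.

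**The case against.** The strongest reply is that this is one loosely worded sentence about non-key variables in a condensed article, on which no decision rule or sample size depends. It might even be shorthand for testing the least-squares-mean contrast. That reading is possible, but an unpaired t-test is a specific two-sample procedure, and the sentence does not naturally describe a model contrast. The conflict lies in what the article states and is not a detail left to another document.

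Several stronger readings might be inferred, and the documents do not support them:

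- **All continuous secondary endpoints are affected.** They are not: total eGFR slope uses the random coefficient model.
- **The t-test discards baseline.** A t-test on change uses baseline by subtraction. What it lacks is adjustment for baseline.
- **Only completers are analysed.** Only those missing the tested visit are lost from that comparison. The planned 10% drop-out should not be added to the precision loss: it would not apply in full at earlier visits, and an MMRM does not fully recover missing values either.
- **The p-value will contradict a stated interval for the difference.** The 95% CI is explicit for the least-squares means. For the difference it is only implied.
- **The loss is measured against the model already planned.** The MMRM covariates are not stated, so the loss holds against a baseline-adjusted model.
- **Type I error is inflated or the t-test is biased.** Neither appeared in the settings tried.
- **Skewed variables will be tested untransformed.** The article does not specify the scale, and an analysis plan could supply transformations.

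**Conclusion.** The point holds for the continuous change-from-baseline secondary endpoints other than the eGFR slopes. Estimate and test come from different procedures, and the named test is the less precise one when set against a baseline-adjusted model. The cost ranges from small (5% of variance at r = 0.9) to material (25% at r = 0.5), with disagreement on significance in about 6% to 18% of simulated trials with a true effect.

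These sizes rest on assumed correlations, equal variances over time and a known compound-symmetric covariance, so they are illustrative. The harm is lost precision and possibly contradictory reporting. The primary conclusion, the key secondary analysis and the sample size are untouched.

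**What to change.** Delete the sentence naming the unpaired t-test. State instead that the between-group difference, its 95% CI and its p-value at each visit all come from the treatment-by-visit contrast of the MMRM. The covariates would be the baseline value, baseline-by-visit, and the four stratification factors (age, eGFR category, diabetes, hypertension). Estimate, interval and test then agree by construction.

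The cost is wording only. The MMRM is already planned, no extra data are needed, and neither the sample size nor alpha changes. Enrollment is complete, but the study is scheduled to run to June 2029, so the change can still be fixed in writing before the analysis.
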